# Statistical analysis

# Statistical methods

(1) Analysis of cognitive function

The average of total WMS-R score at the endpoint will be compared among the GBE/MST, GBE, and placebo groups using one-way analysis of variance (ANOVA) and Tukey's test. The difference between the total score at baseline and at the endpoint will be compared among the three groups using multivariate ANOVA (MANOVA).

(2) Analysis of brain morphology

Total cerebral cortical volume will be calculated from the T1-weighted structural images using the SPM12 software. The average alteration in total volume from baseline to the endpoint will be compared among the three groups. Using the CONN toolbox (https://web.conn-toolbox.org/) implemented in MATLAB, functional connectivity (FC) between two regions of interest (ROIs) within the DMN will be analyzed by means of ROI-to-ROI analysis.

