# Rationale

The primary endpoint of this study is to determine the impact of GBE/MST on cognitive function in healthy adults, which will be assessed by the Wechsler Memory Scale-Revised (WMS-R) after 24 weeks of GBE/MST administration. The WMS-R is designed to indicate a standard deviation of 15 if its normal average score is 100. In the present study, when the estimated alteration rate of the standard deviation was 1%, the difference in the average score was 6. Cohen’s calculation formula with an effect size of 0.4 at a significance level (α) of 0.05 and a detection power (1-β) of 80% yielded a sample size of 44 participants. Considering a dropout rate of 20%, 159 participants will be required (53 participants in each group).

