Standard blood and urine tests will be performed to check for health status. Body measurements, grasping power of both the hands, two-step test, and functional reach test will be performed at baseline and at the endpoint (24 weeks).

Cognitive tests will be completed by the participants at baseline and at the endpoint. The WMS-R and its lower domains will be used to measure total memory function and assess individual function (digit span indicates verbal memory and the tapping span indicates visual memory). Stroop Color and Word Test and Trail Making Test will be employed to assess executive functions such as restraint-related functions and sustained attention, respectively.

Magnetic resonance imaging (MRI: Achieva Intera 3T, Philips Healthcare, Quasar Dual, The Netherlands) will be performed at baseline and at the endpoint. T1 weighted magnetization-prepared rapid acquisition gradient echo (MPRAGE) structural images (matrix: 240 × 240, repetition time: 8.70 ms, echo time: 3.1 ms, flip angle: 8°, field of view: 256 × 256 × 180 mm, 162 slices, voxel size: 0.7 × 0.7 × 0.7 mm, and scan duration: 5 min 15 s) will be acquired to collect 3D structural datasets. Resting state functional MRI (rs-fMRI: T2*-weighted gradient-echo planar imaging, matrix: 64× 64, repetition time: 3000 ms, echo time: 30 ms, flip angle: 90°, field of view: 220 × 220 ×218 mm, 34 slices, voxel size: 3.44 × 3.44 × 3.40 mm and 197 volumes with 5 min superimposition) with closed eyes will be performed to analyze the DMN.

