# Items and methods of evaluation

# Primary endpoint

　To determine the efficacy of GBE/MST in the impact of cognitive function, data of GBE/MST will compare with that of GBE alone and placebo in healthy adults by the Wechsler Memory Scale-Revised (WMS-R) after 24 weeks.

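### The lead WMS-R analysis leaves out the baseline score the trial collects, and a mislabelled, unranked change analysis stands beside it; one baseline-adjusted ANCOVA would be more precise at no cost

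*Protocol*

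**What the plan says.** Primary endpoint (Protocol, Primary endpoint): GBE/MST is compared with GBE alone and placebo "by the Wechsler Memory Scale-Revised (WMS-R) after 24 weeks". Neither a change score nor baseline adjustment is mentioned there.

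Lead analysis (Protocol, Statistical methods, item 1): "The average of total WMS-R score at the endpoint will be compared among the GBE/MST, GBE, and placebo groups". The method named for this is a one-way ANOVA followed by Tukey's test, and no covariate is listed.

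Second analysis of the same variable (same item): "The difference between the total score at baseline and at the endpoint will be compared among the three groups using multivariate ANOVA (MANOVA"). The text does not call it secondary, supportive or a sensitivity analysis.

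Baseline data (Protocol, Methods, Schedule): "Cognitive tests will be completed by the participants at baseline and at the endpoint".

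Planning values (Protocol, Sample size, Rationale): "The WMS-R is designed to indicate a standard deviation of 15 if its normal average score is 100", and "the difference in the average score was 6".

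**The concern.** Adults aged 20 to 64 differ a good deal in memory before anyone takes a capsule. An ANOVA of 24-week scores alone leaves all of that stable variation in the error term. The baseline WMS-R that could remove part of it is already being collected. The price is wider intervals and lower power, in a trial whose power is already short.

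The second analysis adds two smaller problems. MANOVA is a method for several outcomes at once, and the quantity named is one difference per participant. And with two tests of the primary variable and no stated rank, a reader cannot tell from the analysis section alone which one decides if they disagree.

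**Working it through.** **Inputs.** Difference 6, SD 15 (so d = 6/15 = 0.4), α = 0.05, power 80%, 44 evaluable per group, 53 enrolled: all from Sample size, Rationale. Two-sided testing is assumed, as the protocol does not say. The correlation r between baseline and 24-week WMS-R is not given; 0.3 to 0.8 is assumed.

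**The plan's own figure.** Two-sample formula: 2 × (1.96 + 0.84)² / 0.4² ≈ 98.1, so 99 per group, not 44. The 53 is 44 × 1.2 = 52.8, rounded up. The 44 does not reproduce. That is a separate error; 44 is kept here only as the planned evaluable number.

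**Endpoint ANOVA.** Standard error of a pairwise difference = 15 × √(2/44) = 3.198. Noncentrality = 6/3.198 = 1.876, on 132 − 3 = 129 degrees of freedom. Critical value 1.979 for a single comparison; 2.371 for Tukey with three groups (studentized range divided by √2). Noncentral t gives 46% and 31%. Unadjusted 95% half-width = 1.979 × 3.198 = 6.3 points.

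**ANCOVA.** The residual SD becomes 15 × √(1 − r²), with one degree of freedom lost (128). Noncentrality = 0.4/√(1 − r²) × √22.

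| r | Residual SD | Noncentrality | Pairwise power, no multiplicity adjustment | Pairwise power, Tukey | Unadjusted 95% half-width |
|---|---|---|---|---|---|
| none (endpoint only) | 15.0 | 1.88 | 46% | 31% | 6.3 |
| 0.3 | 14.3 | 1.97 | 50% | 35% | 6.0 |
| 0.5 | 13.0 | 2.17 | 58% | 42% | 5.5 |
| 0.7 | 10.7 | 2.63 | 74% | 60% | 4.5 |
| 0.8 | 9.0 | 3.13 | 87% | 77% | 3.8 |

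The omnibus F test with one arm 6 points away behaves similarly: 47% for endpoint only, and 51, 59, 77 and 90% for ANCOVA at the same values of r.

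**Share of the shortfall recovered.** Without multiplicity adjustment the gap to 80% is 80 − 46 = 34 points. ANCOVA recovers 12 of these at r = 0.5 (about a third) and 28 at r = 0.7 (most). With Tukey the gap is 49 points: 11 recovered at r = 0.5, 29 at r = 0.7, 46 at r = 0.8, still just short of 80%.

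**Change score.** Its SD is 15 × √(2(1 − r)), which equals 15 at r = 0.5. Pairwise power without multiplicity adjustment is 35, 46, 67 and 84% at r = 0.3, 0.5, 0.7 and 0.8. So change is worse than endpoint below r = 0.5, equal at 0.5 and better above. ANCOVA beats both at each of these values.

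**The MANOVA label.** With one dependent variable, MANOVA is one-way ANOVA. Read as a two-visit repeated-measures analysis, its group-by-time test is the same change-score ANOVA.

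**Two tests.** Under the null, 40,000 simulated trials per value of r (0.3 to 0.9, 44 per group) put the chance that the endpoint ANOVA or the change ANOVA is significant at 8.9 to 9.5%. Two independent tests would give 1 − 0.95² = 9.75%. A single ANCOVA stays at 5%.

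**The case against.** The strongest reply is that nothing here is invalid. Under randomisation the endpoint ANOVA is unbiased and holds its 5% level, and its standard error already allows for chance baseline imbalance. That stands: the gain is in precision, not validity.

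The size of the gain is also unknown, because r is not in the protocol. A reader might infer that ANCOVA would restore most of the missing power. That needs r of about 0.7 or more, and at 0.3 the gain is only about 4 points. Most of the shortfall comes from planning 44 per group where d = 0.4 needs about 99. Nor is the endpoint comparison always the least efficient choice: at r = 0.5 it ties with the change score, and below that it is better.

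A reader might further infer that the plan nearly doubles its false-positive rate. The protocol states no rule that either test suffices. The Primary endpoint and Rationale sections both point to WMS-R after 24 weeks, and the endpoint ANOVA comes first. The 9 to 10% describes what could happen if the ranking stayed open, not what is planned.

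Finally, it can be said that MANOVA is only a wrong name, since the stated quantity is a difference and the resulting F test is valid. Largely agreed. An analysis of the pair of scores, which would spend effort testing a baseline difference, is not what the sentence describes.

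Leaving such details to a SAP does not answer the point, because the protocol itself names the methods.

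**Conclusion.** The point holds as a matter of efficiency and clarity. The named lead analysis omits a baseline measure that the trial collects, and any positive correlation makes ANCOVA more precise, apart from one lost degree of freedom. With the planned Tukey test the gain in pairwise power at 44 per group runs from about 4 points (r = 0.3) to about 46 points (r = 0.8). This rests on the protocol's difference of 6 and SD of 15, two-sided testing, a linear relation with equal SDs at both visits, and the assumed r. The sample-size error remains. The second analysis is misnamed and unranked; the resulting risk to type I error is open rather than declared. It should be changed, but the existing test is not wrong.

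**What to change.** State one primary analysis: ANCOVA of the 24-week total WMS-R score on randomised group with baseline total WMS-R as covariate, reporting Tukey-adjusted differences between groups with 95% confidence intervals. Either delete the MANOVA or rename it as a one-way ANOVA of change from baseline. Label any unadjusted endpoint or change comparison as supportive only. Adopting ANCOVA does not by itself settle which test decides; the labelling does that.

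The cost is a few lines of text, with no new data or participants. The protocol's section on modifying the protocol lists a change in how efficacy is assessed as an amendment, so approval may be needed. The change should be made before outcome data are seen by arm. If r can be estimated from pooled, blinded data, state it so that the expected gain is no longer an assumption.

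### The 80% power is computed at an unadjusted 0.05, but the primary test is Tukey's over three pairs (about 0.019 each); restate the power, and preferably use F-gated pairwise tests

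*Protocol*

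**What the plan says.** Protocol, Statistical methods, item (1): mean WMS-R totals after treatment "will be compared among the GBE/MST, GBE, and placebo groups". The method named for this comparison is given as "using one-way analysis of variance (ANOVA) and Tukey's test". The text does not say whether Tukey's test is run only after a significant ANOVA.

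Protocol, Primary endpoint: "data of GBE/MST will compare with that of GBE alone and placebo in healthy adults". The section on the rationale of the study design poses the same question. Both name two comparisons, GBE/MST against GBE and GBE/MST against placebo. GBE against placebo is not part of the stated question.

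Protocol, Sample size and rationale: "The WMS-R is designed to indicate a standard deviation of 15", "the difference in the average score was 6", and the calculation is done "at a significance level (α) of 0.05" with 80% power. It arrives at 44 participants, raised to 53 per group (159 in all) for 20% dropout. It does not mention multiple comparisons or name the test behind the figure.

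**The concern.** The sample size and the primary analysis rest on different decision rules. The first spends 5% on one comparison. The second spreads 5% over three, one of which is outside the primary question. A reader who takes the 80% at face value will expect that chance of detecting a 6-point benefit, and the stated analysis does not deliver it. In a trial that is already too small for its stated effect, a non-significant result could be read as absence of effect when it was the likely outcome either way. Part of the loss is also avoidable, because three groups are a special case in which a less conservative procedure keeps the same error guarantee.

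**Working it through.** **Inputs.** From the protocol: difference 6, SD 15, so d = 6/15 = 0.4; alpha 0.05 (taken as two-sided, since sidedness is not stated); power 80%; 44 per group before dropout; three equal groups. Assumed: normal data, equal variances, pooled SD with 3 × 43 = 129 degrees of freedom.

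**1. The plan's own figure.** For two means, n per group = 2 × (1.960 + 0.842)² / d².
- d = 0.4: 15.70 / 0.16 = 98.1, so 99 per group (100 with the t distribution).
- d = 0.6: 15.70 / 0.36 = 43.6, so 44 per group.

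The stated 44 does not follow from 0.4. It matches a two-sided comparison with d = 0.6, a 9-point difference. The 53 is 44 × 1.2 = 52.8.

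**2. Tukey's per-comparison level.** The critical t is q(0.95; 3, 129)/√2 = 2.371, two-sided p = 0.0192. The unadjusted critical t is 1.979.

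**3. Power for GBE/MST versus placebo.** The noncentrality is d × √(n/2) = 0.4 × √22 = 1.876. By normal approximation:
- unadjusted 0.05: P(Z > 1.979 − 1.876) = P(Z > 0.103), about 46%;
- Tukey: P(Z > 2.371 − 1.876) = P(Z > 0.495), about 31%.

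Of the 49-point gap between 80% and 31%, about 34 points come from the sample-size calculation (80% to 46%) and about 15 from Tukey's adjustment (46% to 31%).

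**4. Validity of the F-gated alternative.** If all three means are equal, the F test limits any false claim to 5%. If they are not all equal, at most one pair can still be equal, and that pair is tested at 5%. Family-wise error is therefore held at 5% whatever the true means. This argument does not extend to four or more groups. Simulated error at 44 per group is 0.050 with all means equal, and 0.044 to 0.050 when one group differs by 0.4 to 3 SD. Tukey's error in the latter cases is about 0.019.

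**5. Power of the two procedures** (simulation, 44 per group, endpoint scores without baseline adjustment):

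| True state, d for GBE/MST | Outcome | Tukey | F-gated |
|---|---|---|---|
| 0.4, GBE = placebo | versus placebo | 31% | 38% |
| 0.4, GBE = placebo | both comparisons won | 17% | 29% |
| 0.4, GBE at half effect | versus placebo | 31% | 34% |
| 0.4, GBE at half effect | both comparisons won | 5–6% | 11% |
| 0.6, GBE = placebo | versus placebo | 67% | 75% |

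The last row isolates the mismatch: at the effect that does yield 44, the unadjusted test has 80% power and Tukey 67%. With GBE equal to placebo and d = 0.4, the versus-placebo results are 30% against 36% at 42 per group, and 38% against 45% at 53 per group.

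**6. Size needed for 80% versus placebo at d = 0.4.** About 130 per group with Tukey; about 110 F-gated if GBE equals placebo, or about 125 if GBE has half the effect.

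**7. Baseline adjustment.** The correlation r between baseline and endpoint is not in the protocol. Adjustment turns d into 0.4/√(1 − r²): 0.46 at r = 0.5, 0.56 at r = 0.7 and 0.67 at r = 0.8. With GBE equal to placebo, simulated power versus placebo (Tukey, then F-gated) is 42% and 50%, 60% and 69%, and 77% and 84% respectively.

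**The case against.** Tukey's test after a one-way ANOVA is conventional, prespecified and valid, and it gives simultaneous intervals. Preferring another valid procedure could be called taste. That stands as far as the choice of test goes: Tukey is not an error. It does not rescue the 80%, which is wrong for the stated analysis.

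The gain can also look larger than it is. Versus placebo it is only 2 to 3 points if GBE has half the effect, and the chance of winning at least one GBE/MST comparison barely moves (46% to 47% with GBE equal to placebo). Both stand. Nor is the F-gated procedure best under every success rule. If both wins were required, testing each at 5% with no gate gives about 30% against 29%. A fixed sequence starting with placebo would give that comparison 46% against 38%.

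Two stronger readings are tempting. A reader might infer that ANOVA followed by Tukey pays for multiplicity twice. The protocol does not say that ANOVA gates Tukey, and if it did, the extra cost versus placebo would be under 1 point (31.4% to 30.7%). A reader might also infer that success requires beating both comparators. The protocol says only that GBE/MST is compared with each, so the figures for both comparisons describe one possible claim and not the trial's success rule.

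Finally, the protocol does not name the test behind its 0.05. That it is unadjusted is inferred from the 6/15 effect size and the absence of any multiplicity term.

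**Conclusion.** The point holds in this form. The stated 80% power does not apply to the stated primary analysis: for a 6-point difference with 44 per group it is about 31% under Tukey's test. The larger cause is the sample size, which gives about 46% even without adjustment; Tukey's adjustment takes a further 15 points or so. F-gated pairwise tests recover 2 to 7 of those points versus placebo, and about 6 to 12 for winning both comparisons, at the same 5% family-wise error. On unadjusted endpoint scores they leave the trial far short of 80%.

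These figures assume a two-sided alpha, normal data, equal variances and the protocol's SD of 15. The gains also depend on where GBE lies between placebo and GBE/MST.

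**What to change.** Required: in the sample-size rationale, name the primary comparison and the multiplicity procedure, and restate the power or the number per group for that procedure.

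Preferable: in Statistical methods, replace Tukey's test with wording such as: the three-group F test, from a model for endpoint WMS-R adjusted for baseline WMS-R, is carried out at 5%; if it is significant, GBE/MST versus placebo and GBE/MST versus GBE are each tested at two-sided 5%; GBE versus placebo is reported as secondary.

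Cost: a few lines of text, with no added visit or measurement. Pairwise claims would need a significant F, and the 95% intervals would not be simultaneous. Baseline adjustment is a separate change that uses data already collected, and its benefit depends on a correlation the protocol does not give. If Tukey's test is kept for its simultaneous intervals, only the power statement needs correcting. None of this replaces a corrected sample size.

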# Methos and period of the study

# Study design

1. Study design
   1. **Control**

Placebo

- 1. **Randomization**

Double-blind

- 1. **Comparison**

Randamized placebo-controlled

1. **Rationale of the study design**

The primary aim of this study is to determine the efficacy of GBE/MST in the impact of cognitive function when compared with that of GBE alone and placebo in healthy adults using neuropsychological assessments. The study also aims to evaluate the alterations in the default mode network (DMN) after 24 weeks of GBE/MST administration and compare them with the baseline data.

# Methods

1. Intervention

〇Active

・GBE/MST capsule (commercially known as “Brain assist ®︎”)

Ginkgo biloba extract, sesame oil, Piper longum extract, reduced sugar syrup, refined fish oil containing docosahexaenoic acid with gelatin, spice extract, glycerin, glycerin fatty acid ester, beeswax, caramel color, vegetable lecithin from soybean

4 kcal, proteins: 0.2g, lipids: 0.3g, carbohydrates: 0.2g, salt: 0.0008g

・GBE capsule (commercially known as “Icho-ba Ekisu”)

Ginkgo biloba extract, reduced sugar syrup, gelatin, glycerin fatty acid ester, caramel color, tocotrienol lecithin from soybean

5 kcal, proteins: 0.2g, lipids: 0.4g, carbohydrates: 0.2g, salt: 0.0009g

Both have a dosage of two capsules per day. Both the products will be provided by Ohki Pharmaceutical Company and will have similar shapes, colors, and tastes. The package containing the products will not have any information to avoid participant bias.

〇Placebo

Placebo will be made in matched for size, color and taste to the GBE/MST capsule and GBE capsule.

Reduced sugar syrup, refined fish oil containing docosahexaenoic acid with gelatin, spice extract, glycerin, glycerin fatty acid ester, beeswax, caramel color, vegetable lecithin from soybean

5 kcal, proteins: 0.2g, lipids: 0.5g, carbohydrates: 0.1g, salt: 0.0009g

1. **Dosage and administration**

Participants in the GBE/MST group will consume two capsules of the GBE/MST supplement. Participants in the GBE group will consume two capsules of GBE supplement. Participants in the placebo group will consume two capsules of placebo.

1. **Adverse effects and cessation criteria**

The adverse effects will be screened throughout the study period. Headache, dizziness, tinnitus, diarrhea, nausea, gastrointestinal symptoms, high blood pressure, excessive thirst, dyspnea, chest pain, bradycardia, and upper respiratory infection have been reported as adverse effects of GBE [5]. Interestingly, participants consuming GBE showed a lower incidence of adverse events when compared with those consuming a placebo [10]. The study will be terminated if any grade 3 adverse event is reported. If a participant shows any adverse events and requests a refusal, the study will be terminated.

1. **Schedule**

At registration, written informed consent will be obtained from the participants. Subsequently, cognitive function will be evaluated using the MoCA-J. Participants with a score of ≧26 will be eligible for inclusion.

Standard blood and urine tests will be performed to check for health status. Body measurements, grasping power of both the hands, two-step test, and functional reach test will be performed at baseline and at the endpoint (24 weeks).

Cognitive tests will be completed by the participants at baseline and at the endpoint. The WMS-R and its lower domains will be used to measure total memory function and assess individual function (digit span indicates verbal memory and the tapping span indicates visual memory). Stroop Color and Word Test and Trail Making Test will be employed to assess executive functions such as restraint-related functions and sustained attention, respectively.

Magnetic resonance imaging (MRI: Achieva Intera 3T, Philips Healthcare, Quasar Dual, The Netherlands) will be performed at baseline and at the endpoint. T1 weighted magnetization-prepared rapid acquisition gradient echo (MPRAGE) structural images (matrix: 240 × 240, repetition time: 8.70 ms, echo time: 3.1 ms, flip angle: 8°, field of view: 256 × 256 × 180 mm, 162 slices, voxel size: 0.7 × 0.7 × 0.7 mm, and scan duration: 5 min 15 s) will be acquired to collect 3D structural datasets. Resting state functional MRI (rs-fMRI: T2*-weighted gradient-echo planar imaging, matrix: 64× 64, repetition time: 3000 ms, echo time: 30 ms, flip angle: 90°, field of view: 220 × 220 ×218 mm, 34 slices, voxel size: 3.44 × 3.44 × 3.40 mm and 197 volumes with 5 min superimposition) with closed eyes will be performed to analyze the DMN.

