# Porpose

This study aims to investigate the effectiveness of a mixture of Ginkgo biloba extract (GBE), sesame extract, and turmeric oil (GBE/MST) on the cognitive function of healthy adults.

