GBE has two active components, flavonoids and terpene lactones. Flavonoids have been reported to accumulate in the blood serum [4]. Since major effects of flavonoids include reduction in the inflammatory response, oxidization, and platelet aggregation in vivo, these effects are expected to play important roles in inhibiting damage to the vascular endothelial cells and improving the peripheral blood flow [5]. Terpene lactones have been reported to infiltrate the central nervous system (CNS) but are quickly metabolized, resulting in very low concentrations in the CNS [4]. Since terpene lactones were reported to reduce caspase-3 activation and amyloid-β aggregation and protect the mitochondrial membrane, they can be expected to protect the neurons from apoptosis and amyloid-β toxicity [6]. However, since the concentration of terpene lactones in the CNS might be very low in vivo [4, 7], the effect of GBE on cognitive function may be exclusively explained by improvement in the cerebral blood flow. Administration of a mixture of GBE, sesame seed extract, and turmeric oil (GBE/MST) was reported to increase the concentration of terpene lactones in the mouse brain [7]. The aforementioned study reported that the concentration of bilobalide, a terpene lactone, in the brain was not significantly different between the GBE alone and GBE/MST groups (mean ± standard error of the mean: 1.30±0.31 and 0.75±0.24 μg/mg, respectively). Ginkgolide A, another terpene lactone, was detected in the GBE/MST group, but it was not detected in the GBE alone group. The GBE/MST supplement is currently available in the Japanese market, although its scientific effects have not been validated. Since low bioavailability of GBE in the brain may be a possible cause of its faint effect on the cognitive function, it might be of great interest to investigate whether the efficacy of GBE is improved by administration in the form of GBE/MST in healthy adults.

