・Inform that the examination can stop anytime during the procedure if a participant will feel any abnormalities.

2. Since the MRI apparatus has strong magnetic field, metallic materials can be pulled and may physically injure a participant. Counterplans are described below:

・Metallic material without anchoring must not be stored in the MRI room.

・The exclusinve stuffs of MRI must control the procedures in the MRI room which has protective methods against expecting risks.

3. There is a possibility of finding any critical diseases, such as brain tumore, brain absess, brain hemorrhage, brain infarction, brain artery aneurysm, arteriovenous malformation, etc., by analysis of MRI. If any of such abnormality will be found, an investigator will inform the participant about to ask a doctor.

4. During MRI procedures, undesired noise, magnetic field, change of body temperature, and unconfortable position in narrow space may cause discomfort. As counterplan of discomfort, a participant can use a buzzer for alart any bad feeling. If a buzzer sounds, an operator must stop the procedure, and a doctor must check a participant’s condition. In case of difficultiness, the MRI procedure can be cancelled.

Risks and adverse events regarding GBE and GBE/MST

　GBE, sesame extract, and turmeric oil have been used as suppliments, and their safety has been established. No critical adverse event was reported. Digestive symptoms and thirsty have been reported as side effects. These symptoms will diminish after 3-4 days of cessation. If such side effects are strong, participation of this study can immediately be stopped.

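### The GBE/MST capsule as listed is not the mixture the protocol names, and the three capsules differ in background ingredients, so the contrasts compare whole products and cannot be attributed to sesame plus turmeric, to bioavailability or to GBE alone

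*Protocol*

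**What the plan says.** The Protocol's purpose section (headed Porpose) sets out to study the "effectiveness of a mixture of Ginkgo biloba extract (GBE), sesame extract, and turmeric oil (GBE/MST) on the cognitive function of healthy adults". The Purpose paragraph of the Abstract describes the same mixture. Backgrounds gives the mouse experiment behind it: "Administration of a mixture of GBE, sesame seed extract, and turmeric oil (GBE/MST) was reported to increase the concentration of terpene lactones". It then asks whether the efficacy of GBE improves when GBE is given as GBE/MST. The risk section (Burdens, foreseeable risks) rests its safety statement on the same components: "GBE, sesame extract, and turmeric oil have been used as suppliments".

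The Intervention part of Methods lists the capsules:

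- GBE/MST: "Ginkgo biloba extract, sesame oil, Piper longum extract, reduced sugar syrup, refined fish oil containing docosahexaenoic acid with gelatin, spice extract", then glycerin and further excipients.
- GBE: "Ginkgo biloba extract, reduced sugar syrup, gelatin, glycerin fatty acid ester, caramel color, tocotrienol lecithin from soybean".
- Placebo: the same run of ingredients that closes the GBE/MST list, namely "reduced sugar syrup, refined fish oil containing docosahexaenoic acid with gelatin, spice extract, glycerin, glycerin fatty acid ester, beeswax, caramel color, vegetable lecithin from soybean".

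Both active products are identified by commercial names and taken as two capsules a day. The two actives are to be similar in shape, color and taste, and the placebo is to match them in size, color and taste. Nothing is promised about background ingredients. The amount of Ginkgo extract is stated for neither active.

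The Rationale of the study design and the Primary endpoint compare GBE/MST with GBE alone and with placebo.

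**The concern.** The intervention is described in two ways that do not agree. Four places name turmeric oil. The capsule list shows no turmeric and instead shows a Piper longum extract for which the protocol gives no rationale.

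In addition, the GBE capsule is not the GBE/MST capsule with the added components taken out, nor is it the placebo with Ginkgo put in. The trial's distinctive question is whether the mixture does more than GBE. If the arms also differ in fish oil and spice extract, a difference between them cannot be credited to sesame and turmeric, or to the higher brain concentration of terpene lactones that motivates the study. Nor can a difference between GBE and placebo be read as the effect of GBE by itself. At stake is what the report may conclude, and whether the risk information and the exclusion for allergy to the study materials refer to what is actually in the capsules.

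**Working it through.** No sample size, power or alpha figure bears on this point, so there is no design figure to reproduce. The check sets the lists side by side.

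**Step 1. Named against listed.** Named in the Abstract, purpose section, Backgrounds and risk section: Ginkgo, sesame extract (sesame seed extract in Backgrounds), turmeric oil. Listed in Methods for GBE/MST: Ginkgo, sesame oil, Piper longum extract, DHA fish oil, spice extract, excipients. Turmeric is named but not listed. Piper longum is listed but not named.

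**Step 2. The three capsules in Methods.**

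| Item | GBE/MST | GBE | Placebo |
|---|---|---|---|
| Ginkgo extract | yes | yes | no |
| Sesame oil | yes | no | no |
| Piper longum extract | yes | no | no |
| Turmeric | not listed | not listed | not listed |
| DHA fish oil with gelatin | yes | no (gelatin alone) | yes |
| Spice extract | yes | no | yes |
| Glycerin, beeswax | yes | no | yes |
| Soybean lecithin | vegetable | tocotrienol | vegetable |
| Sugar syrup, glycerin fatty acid ester, caramel color | yes | yes | yes |
| Stated lipids | 0.3 g | 0.4 g | 0.5 g |
| Amount of Ginkgo extract | not given | not given | none listed |

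**Step 3. Differences by contrast.**

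- GBE/MST versus GBE: sesame oil, Piper longum, DHA fish oil, spice extract, glycerin, beeswax and type of lecithin.
- GBE versus placebo: Ginkgo, with DHA fish oil, spice extract, glycerin and beeswax absent from GBE, and type of lecithin.
- GBE/MST versus placebo: Ginkgo, sesame oil and Piper longum. The remaining names are identical.

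**Step 4. Does the shared list mean matched amounts?** If lipids are rounded to one decimal on the same serving basis, GBE/MST has 0.25 to 0.35 g and placebo 0.45 to 0.55 g. The gap is at least 0.45 − 0.35 = 0.10 g and at most 0.55 − 0.25 = 0.30 g, so rounding does not explain it. The GBE/MST figure also includes the sesame oil. This does not show that the fish oil differs, since other lipids could. It does mean that equal amounts are not shown.

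**Step 5. What each contrast estimates.** Assume additive effects for illustration. Write g_M and g_G for the Ginkgo effect in the two actives, m for the added components (including any effect on bioavailability), b_M and b_P for the background in GBE/MST and placebo, and l for the background specific to GBE. Then:

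- GBE/MST − GBE = (g_M − g_G) + m + (b_M − l)
- GBE − placebo = g_G + (l − b_P)
- GBE/MST − placebo = g_M + m + (b_M − b_P)

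Each left-hand side is estimated validly under randomisation. The first equals m only if g_M = g_G and b_M = l. The second equals g_G only if l = b_P. The third equals g_M + m only if b_M = b_P. The document establishes none of these equalities. If b_M and b_P both exceed l, the first contrast widens and the second narrows, which is the pattern the hypothesis predicts. No term can be given a number, because no ingredient amounts are stated.

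**The case against.** The strongest reply is that the plan compares products. Methods identifies both actives as marketed goods, the primary endpoint compares GBE/MST with GBE and with placebo, and no section promises to isolate sesame, turmeric or ginkgolides. Randomisation makes the product comparisons valid. That stands: the product contrasts are not biased, and the limit falls on interpretation. The reply does not reach Backgrounds, where the mechanism is the stated reason for the trial, or the wording that calls the comparator GBE alone.

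The lists may also be abbreviated or imperfectly translated. GBE declares 0.4 g of lipid, more than GBE/MST, although its list names no oil. This too stands, and is why the finding is worded as listed and asks for reconciliation. Confounding by DHA is not firmly established.

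A reader might infer more on three points, and the document does not support it:

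- That GBE/MST versus placebo cannot test turmeric whichever way the list is read. This assumes that spice extract is the same substance in both products, which is not stated, and it overlooks that Piper longum may be a naming error for turmeric.
- That GBE/MST versus placebo is the one matched contrast and should alone carry the efficacy claim. The match is of names only, and the lipid figures differ.
- That the two actives contain different amounts of Ginkgo. Scientific rationale reports larger differences at 240 than at 120 mg/day, so the amount matters by the protocol's own account. But an unstated amount is an omission and does not show inequality.

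**Conclusion.** The concern holds as a contradiction about what is tested and a limit on attribution. Turmeric oil is named in four places and appears in none of three ingredient lists. Piper longum appears once, without explanation. As listed, two of the three pairwise contrasts (those involving GBE) differ in DHA fish oil and spice extract, and the third shares names without shown equality of amounts.

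The size of any effect on interpretation is unknown. The conclusion assumes only that the lists are read as written, and a specification showing otherwise would change it. It would be wrong to infer that the randomised comparisons are invalid: the tests, the error rate and the sample size are untouched by this point. Which composition is correct cannot be settled from the document.

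**What to change.** 1. Reconcile the Abstract, purpose section, Backgrounds, Methods and risk section, and the consent text, with the manufacturer's specification. Settle whether turmeric is present, whether Piper longum is correct, what spice extract is in each product, and the GBE content of both actives.
2. Describe the three arms by their actual contents.
3. State that all three pairwise contrasts compare whole products. GBE/MST versus GBE is not to be attributed to sesame, turmeric or bioavailability, and GBE versus placebo is not to be read as the effect of GBE alone, unless the specification shows matched background ingredients.

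The primary comparisons in the Rationale of the study design and Primary endpoint sections stay as planned, and no reformulation is proposed. The cost is a query to the manufacturer, revised wording in the protocol and consent, the Ethics Committee review and approval that the protocol requires for any change of plan, and a narrower mechanistic claim.
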